**Secondary Effectiveness Outcomes (compared between intervention and control groups)**				
Time to First Visit	Number of days elapsed between discharge and first primary care appt	EHR/admin	LR	Once/patient
Acute Care Utilization	# of ED, hospital, or urgent care visits during the 6 months preceding and 6 months following enrollment	PT	S, Qual	At 2, 4, and 6 months
Substance Use	Self-reported frequency and amount of substance use	PT	S, Qual	At 2, 4, and 6 months

**Abbreviations**: CT = clinical team (PCP, hospitalists, social workers). IT = IntACT team members. S = Survey. Qual = qualitative interviews or focus groups, Admin = administrative data. PT = patient. EHR = electronic health record. LR = logistic/linear regression

Primary effectiveness outcomes will be compared between intervention and control groups and include: 1) the percentage of participants who attend a follow-up visit (e.g., primary care, specialty care, SUD care) within 14 days of discharge, and 2) the percentage of participants with evidence of SUD care engagement at 2, 4, and 6 months following discharge, including attendance at scheduled visits and/or documentation of medication for substance use disorder receipt. Secondary effectiveness outcomes include: 1) time to first follow-up visit after hospital discharge; 2) self-reported substance use; and 3) acute care utilization including hospital readmission, ED visits, and urgent care visits. These outcomes will be assessed using a combination of administrative data review and patient self-report using the Timeline Followback method, an established framework for assessing recent substance use patterns [46,47].

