**Methods:**

The IntACT pilot study is a single-site randomized controlled trial that aims to assess the feasibility and preliminary effectiveness of a primary care-based Interdisciplinary Addiction Care Transition (IntACT) team. IntACT deploys from a partnering primary care clinic to the hospital to meet patients with SUD while they are admitted, then follows them after discharge for four months to facilitate linkage to and retention in follow-up care. The pilot study will randomize 75 hospitalized patients with SUD to receive IntACT or Usual Care, assessing both implementation and effectiveness outcomes over a six month study period. Primary outcomes include implementation measures (e.g., reach, acceptability, feasibility, and cost) assessed using a mixed methods approach, as well as preliminary measures of effectiveness including successful linkage to follow-up medical and/or SUD care after hospitalization and retention in treatment. Secondary effectiveness measures include time to first post-discharge follow-up visit, substance use patterns, and acute care utilization (e.g., hospital readmissions). The IntACT study will also enroll 20 clinicians from hospital and outpatient settings who interact with IntACT while providing patient care to provide input on intervention feasibility, appropriateness, and acceptability. Study design and procedural elements will also be assessed for feasibility and acceptability.

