**Fig 1 pone.0359281.g001:**
[figure not shown]
Participant timeline of enrollment, interventions, and assessments. Abbreviations: SF-12 = 12-Item Short Form Survey; TAPS = Tobacco, Alcohol, Prescription Medication, and Other Substances Tool; PHQ-9 = Patient Health Questionnaire-9; GAD-7 = Generalized Anxiety Disorder-7; TLFB = Timeline Follow-Back; IntACT = Interdisciplinary Addiction Care Transition team.

The IntACT trial’s secondary objectives are to measure the intervention’s effects on: 1) time from discharge to first completed follow-up medical or SUD visit, 2) substance use patterns, and 3) rates of acute care utilization (i.e., hospital readmission, emergency department [ED] or urgent care visits). Including a broad range of effectiveness outcomes will help to determine the feasibility of the study’s assessment approach and outcomes selection for a future fully-powered trial.

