### Intervention

Participants randomized to IntACT will receive usual inpatient and outpatient services plus an interdisciplinary addiction care transition team consisting of a Board-certified addiction specialist, a nurse care manager, and a peer support specialist. The IntACT intervention provides: 1) in-hospital discharge planning support, 2) proactive post-discharge outreach and care coordination, 3) intensive care management and peer support, and 4) interim SUD and medical care coordination for up to four months post-randomization, with the goal of facilitating transition to longitudinal community-based care.

Upon randomization to the IntACT study arm, a member of the IntACT team (either peer navigator, clinician, or care manager) will deploy in person to the hospital to meet the participant, introduce their role, and exchange contact information. Initial contact will be made within 2 business days of randomization. The IntACT team member will discuss potential discharge needs with the participant and offer to facilitate any needed follow-up care at a partnering primary care/addiction medicine clinic or at a community site of the participant’s choosing. A one-page contact sheet will be provided to the patient with a IntACT team cell phone number and contact information for both our peer support specialist and care manager during the initial visit. If the patient leaves the hospital after randomization and before a member of the IntACT team can meet them, remote (e.g., telephone, text) outreach will be provided to complete the initial clinical meeting.

The IntACT team will continue to communicate with the patient and the care team ad hoc during the remainder of the hospitalization to address any care coordination needs that arise. At weekly IntACT clinical team meetings, the team will review the new participant’s hospital course, medications, and discharge needs. Ensuing discussion will focus on how best to leverage the interdisciplinary IntACT team to improve post-discharge care, including linkage to community supports, addressing biopsychosocial barriers to follow-up, and ensuring appropriate access to SUD and medical care.

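### Table 2 times the first visit to primary care only, which contradicts the secondary objective (first completed medical or SUD visit) and the wording used elsewhere in the article

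*Protocol article*

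**What the plan says.** The Protocol article states this outcome in four places.

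- Objectives, secondary objective 1: "time from discharge to first completed follow-up medical or SUD visit".
- Abstract, Methods: "time to first post-discharge follow-up visit".
- Outcomes, text below Table 2: "time to first follow-up visit after hospital discharge".
- Outcomes, Table 2, row Time to First Visit: "Number of days elapsed between discharge and first primary care appt". The source is EHR or administrative data and the method is regression.

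The paragraph below Table 2 also shows how the authors use the term follow-up visit. For the primary linkage outcome it counts participants who "attend a follow-up visit (e.g., primary care, specialty care, SUD care) within 14 days of discharge". The Care Linkage row of Table 2 likewise counts any outpatient visit.

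On setting, the Abstract says that "IntACT deploys from a partnering primary care clinic to the hospital to meet patients with SUD while they are admitted". The Intervention section says the team will offer to "facilitate any needed follow-up care at a partnering primary care/addiction medicine clinic or at a community site of the participant’s choosing". Usual Care follow-up depends on insurance and patient preference, and Usual Care patients may use the partnering clinic through ordinary referral. The Statistical analysis section makes complete-case analysis the primary approach to missing data.

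**The concern.** Table 2 and secondary objective 1 describe different variables. The objective stops the clock at the first completed visit of either kind, medical or SUD. The table stops it only at primary care. Someone abstracting records from Table 2 would collect something other than what the objective asks for.

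Three things are at stake. First, the objective would go unanswered. Second, a patient could count as linked within 14 days on the primary outcome and still have a first-visit time well beyond 14 days, or none at all. Third, if the arms differ in where patients are first seen, that difference would show up as a difference in speed. The article says the broad set of effectiveness outcomes is there partly to guide outcome selection for the full trial. An outcome with two definitions serves that purpose poorly and leaves room to choose between them once data are in.

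**Working it through.** **1. The definitions side by side**

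| Place | Event that stops the clock |
|---|---|
| Secondary objective 1 | first completed medical or SUD visit |
| Abstract | first follow-up visit, type not restricted |
| Outcomes text | first follow-up visit, type not restricted |
| Table 2 | first primary care appointment |

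One of the four is narrower, and no sentence explains why. The Care Linkage row of the same table uses a broad term, so the narrow wording is not simply how the table refers to visits.

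**2. What it does to single patients (hypothetical)**

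- SUD programme on day 5, primary care on day 40: the value is 5 under the objective and 40 under Table 2, a gap of 40 − 5 = 35 days. The same patient is a success on the 14-day primary outcome.
- SUD programme on day 5, no primary care visit: the value is 5 under the objective. Table 2 gives no value, and a complete-case analysis would drop a patient who did link to care.

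**3. What it can do to the comparison**

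The article gives no figure for this outcome, so there is none to reproduce. The following is an illustration.

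Inputs from the article: 75 patients at 3:2, so 75 × 3/5 = 45 IntACT and 75 × 2/5 = 30 Usual Care; complete-case analysis.

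Assumptions: times to a primary care visit and to any other medical or SUD visit are independent and exponential. The total visit rate is h = 1/20 per day in both arms, so there is no true difference in time to any visit. A share s of that rate is primary care. Follow-up is F = 180 days.

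The primary care rate is λ = s·h. The complete-case mean among patients with a primary care visit by day F is

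m(s) = 1/λ − F·e^(−λF) / (1 − e^(−λF)).

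- s = 0.4: λ = 0.020, m = 44.9 days
- s = 0.5: λ = 0.025, m = 38.0 days
- s = 0.6: λ = 0.030, m = 32.5 days
- s = 0.7: λ = 0.035, m = 28.2 days
- s = 0.8: λ = 0.040, m = 24.9 days
- Any visit (λ = 0.050): m = 20.0 days in both arms, which is the objective's definition

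Simulating 4,000 trials of 45 versus 30 patients gives the same picture:

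| Primary care share, IntACT / Usual Care | Mean days under Table 2, IntACT / Usual Care | Difference (true value 0) |
|---|---|---|
| 60% / 40% | 32.6 / 45.0 | about −12 |
| 70% / 40% | 28.2 / 45.0 | about −17 |
| 80% / 40% | 24.8 / 44.8 | about −20 |
| 50% / 50% | 37.9 / 37.9 | about 0 |
| 40% / 60% | 44.7 / 32.6 | about +12 |

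Negative values favour IntACT. With equal shares there is no bias between arms, but both means are about 38 − 20 = 18 days longer than the quantity in the objective. In this model at most about 3% of patients have no primary care visit by day 180, because everyone would reach primary care eventually. If some patients link only to SUD care, the loss under Table 2 would be larger.

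**The case against.** The strongest reply is that three statements are broad or unrestricted and only one abbreviated table cell is narrow. The article says its outcomes are represented in Table 2, but not that the table overrides the text. A reader might infer that the narrow version is settled and will be used. The documents do not support that. They support an unreconciled conflict, which is enough to need correcting.

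A reader might also infer that Table 2 favours IntACT because the team is based in primary care. That is plausible but not established. The article gives no visit-type shares for either arm. IntACT patients may be followed "at a partnering primary care/addiction medicine clinic or at a community site" of their own choice. The partnering clinic also practises addiction medicine, so a first IntACT visit could be an SUD visit that Table 2 does not count. Usual Care patients may attend the same clinic. The bias could be absent or run against IntACT.

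Nor should much be made of the table's abbreviation for appointment. The row is labelled as time to a visit, so reading it as an unattended booking is strained. The objective does say completed, and the table might as well say so too.

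Finally, this is a secondary outcome in a pilot that is expressly not powered for effectiveness, and the primary linkage outcome already counts any outpatient visit. That limits the consequence but does not remove the contradiction.

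**Conclusion.** The point holds as an inconsistency in the outcome definition. Table 2 restricts Time to First Visit to primary care, while the objective covers medical or SUD visits and the Abstract and Outcomes text carry no such restriction. Followed as written, Table 2 gives later or missing times to patients who first link to SUD or specialty care. It does not answer the objective, and it can disagree with the primary linkage outcome for the same patient. This conclusion rests on the text alone.

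Bias between arms is a possible further consequence. Its size and sign depend on visit-type shares that the article does not give. Under the assumptions above, it runs from an IntACT advantage of about 12 to 20 days, through zero, to a disadvantage of about 12 days. These figures show sensitivity and do not predict the result.

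**What to change.** Change the Table 2 measure for Time to First Visit to days from discharge to first completed outpatient medical or SUD visit, in line with secondary objective 1. Record the type of that first visit. If time to primary care is of interest in its own right, report days to first completed primary care visit as a separately labelled additional outcome.

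The cost is one line in Table 2 and an update to the abstraction form, with the same EHR and administrative source. The downside is that visit type must be coded during abstraction.

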### Procedures and assessments

Key study-related procedures include participant enrollment and completion of iterative outcome assessments during and after the 4-month intervention period. These are outlined in Table 1.

**Table 1 pone.0359281.t001:** Assessment timeline for patient participants.

Study Procedure	Baseline	Month 2	Month 4	Month 6
Eligibility confirmation and consent	X			
Baseline survey (demographics and substance use history questionnaire)	X			
Study visit/ follow-up contact	X	X	X	X
SF-12	X	X	X	X
TAPS (Baseline only)	X			
PHQ-9	X	X	X	X
GAD-7	X	X	X	X
TLFB (Substance Use and ED/Hospital Encounters; Follow-up visits only)		X	X	X
Qualitative interview (n = 15; IntACT arm only)				X
Adverse event assessment		X	X	X

*Abbreviations: SF-12 = 12-Item Short Form Survey; TAPS = Tobacco, Alcohol, Prescription Medication, and Other Substances Tool; PHQ-9 = Patient Health Questionnaire-9; GAD-7 = Generalized Anxiety Disorder-7; TLFB = Timeline Follow-Back; IntACT = Interdisciplinary Addiction Care Transition team.*

If a potential participant meets eligibility criteria during the screening process, the research coordinator will explain the study objectives, procedures, and the randomized nature of the trial; assess interest in participation; and conduct a formal written informed consent process for those who wish to enroll. Once consented, participants will complete a baseline survey to finalize enrollment. Individuals unable to provide informed consent due to acute intoxication, withdrawal, medical illness, or psychiatric symptoms causing decisional impairment will not be enrolled. Trained research staff will re-approach these patients a minimum of 4 hours later to reassess their ability to consent to study participation. This assessment will be based on gestalt of the patient’s clinical status (e.g., intubation, sedation) and ability to answer questions in a linear and comprehensible manner. Once a participant is enrolled in the study, they will be randomized to receive the intervention or Usual Care.

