### Statistical analysis

Consistent with National Institutes of Health recommendations for pilot and feasibility studies, this trial is not designed for statistical power to definitively test effectiveness hypotheses [48]. Quantitative data related to implementation will be presented descriptively. Linear and logistic regression modelling will be used, as appropriate, to compare effectiveness outcomes between the control and intervention groups in order to test the feasibility of our assessment and analytic strategies (Table 2). Complete case analysis will be used as a primary approach to missing data. If there is a large amount of missing data, multiple imputations will be used to mitigate the effects of missing data.

Semi-structured interviews related to IntACT’s implementation will be recorded, transcribed and de-identified. Subsequently, the transcripts will summarized and deductively analyzed according to the domains of the PRISM implementation framework using a Rapid Qualitative Analytic approach [49–51]. Qualitative themes pertaining to intervention implementation will be identified from the summaries and compared with quantitative data to identify cross-cutting themes related to intervention acceptability, appropriateness, and feasibility. Mixed methods research frameworks (e.g., joint display) will be used to draw inferences from the combined quantitative and qualitative implementation data [52,53].

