Another strength of this study is that the intervention spans care settings that are often siloed during post-hospitalization care transitions [15]. While the IntACT team is based in primary care, the intervention begins with in-reach to meet enrolled participants while they are still hospitalized. This step enables one clinical team to provide continuity of care before discharge, during the immediate post-hospitalization period, and then longitudinally for the following four months. There are numerous theoretical advantages to this approach, including providing interdisciplinary support during discharge planning, establishing rapport and exchanging accurate contact information with patients prior to discharge, and allowing for stronger lines of communication between inpatient and outpatient care settings. However, these advantages come at the cost of dedicated effort required to mobilize to the hospital and provide intensive care coordination after discharge. The IntACT study includes measures of feasibility that include cost estimates and post-discharge acute care utilization that will help to elucidate the financial sustainability of the model and which can inform future adequately-powered cost-effectiveness studies.

Finally, the team-based design of IntACT is a key feature that will be evaluated in this pilot study. Interdisciplinary teams bring complementary expertise that can confer synergy to complex clinical episodes like SUD care transitions. However, there are also additional investments required by health systems to support staff, training, and infrastructure (e.g., cell phone) for team-based care. The IntACT study includes both quantitative and qualitative assessments with intervention team members, clinicians who interact with the intervention, and patient participants to learn about the feasibility, unique benefits, and required investments for a team-based care transition intervention. The cost analysis will add another element of assessment to generate hypotheses about the relative benefits and costs of team-based models that can be studied in future comparative effectiveness studies with other types of interventions such as individual (e.g., a single care manager) models. The study’s use of established implementation science frameworks like PRISM and RE-AIM provide tools to contextualize our findings and inform conclusions about the implementation of team-based care to support SUD care transitions in general medical settings.

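### Table 2 defines the between-arm acute care outcome over windows before and after enrollment without saying how the earlier window is used; the post-enrollment count adjusted for the prior count should be the stated outcome

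*Protocol article*

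**What the plan says.** In the Outcomes section, Table 2 gives one measure for acute care utilization: the number "of ED, hospital, or urgent care visits during the 6 months preceding and 6 months following enrollment". The row sits under the heading "Secondary Effectiveness Outcomes (compared between intervention and control groups", so the measure is meant for a comparison of arms. The table does not say how the two windows are combined or whether they are kept apart.

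Three other places describe the same outcome with no window before enrollment:

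- The secondary objectives (text after the Fig 1 legend) concern the intervention's effect on "rates of acute care utilization (i.e., hospital readmission, emergency department [ED] or urgent care visits".
- The text below Table 2 lists "acute care utilization including hospital readmission, ED visits, and urgent care visits".
- The Discussion speaks of "measures of feasibility that include cost estimates and post-discharge acute care utilization".

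On the model, the Statistical analysis section says "Linear and logistic regression modelling will be used, as appropriate, to compare effectiveness outcomes between the control and intervention groups". It neither lists nor rules out covariates.

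**The concern.** Visits before enrollment took place before assignment, so the intervention cannot change them. They can be useful in a comparison of arms as baseline information about each patient. Inside the outcome they mainly add variation between patients. Any SUD and any medical admission qualifies, so prior utilization will plausibly differ widely from patient to patient.

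As worded, Table 2 allows at least three analyses: a 12-month total, a before-after change, or a post-enrollment count with the prior count as covariate. They differ in precision, and the total also differs in what a ratio estimate means. The article says that its range of effectiveness outcomes will help decide outcome selection for the later fully powered trial, and its Discussion ties acute care utilization to the model's financial sustainability. An estimate that is noisier than it need be, or a ratio pulled toward 1, would inform those decisions poorly.

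**Working it through.** **Inputs.** The document gives 75 patients (Recruitment and eligibility) at 3:2 (Study design): 75 × 3/5 = 45 IntACT and 75 × 2/5 = 30 Usual Care. It states no variance, correlation, effect size or visit rate for this outcome, so there is no figure of its own to reproduce. What follows is assumed: equal variance in the two windows (set to 1), and a within-patient pre/post correlation rho between 0.2 and 0.7.

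**Step 1, variance per patient under each reading.**

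- Sum of the two windows: 2(1 + rho)
- Post-enrollment count, unadjusted: 1
- Change (post minus pre): 2(1 − rho)
- Post-enrollment count adjusted for the prior count: 1 − rho²

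**Step 2, ratio to the adjusted analysis.** Since 1 − rho² = (1 − rho)(1 + rho), the sum has 2/(1 − rho) times the adjusted variance, the change score 2/(1 + rho) times, and the unadjusted post count 1/(1 − rho²) times.

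| rho | Sum / adjusted | Change / adjusted | Post only / adjusted |
|---|---|---|---|
| 0.2 | 2.50 | 1.67 | 1.04 |
| 0.3 | 2.86 | 1.54 | 1.10 |
| 0.5 | 4.00 | 1.33 | 1.33 |
| 0.7 | 6.67 | 1.18 | 1.96 |

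These ratios do not depend on the sample size or the effect size. The change score is worse than ignoring baseline whenever 2(1 − rho) > 1, that is, when rho is below 0.5.

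**Step 3, effect on a ratio if the windows are summed.** Let q be the control-arm mean before enrollment divided by the mean after it. A true post-enrollment rate ratio RR then appears as (q + RR)/(q + 1). For RR = 0.70:

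- q = 0.5: (0.5 + 0.70)/1.5 = 0.80
- q = 1: (1 + 0.70)/2 = 0.85
- q = 2: (2 + 0.70)/3 = 0.90

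**Step 4, effect on the absolute difference.** The expected pre-enrollment mean is the same in both arms, so it cancels from the difference in means. The sum therefore estimates the same absolute difference as the post-enrollment count, with more noise.

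**Step 5, check with counts.** The formulas above do not use the shape of count data, so gamma-Poisson counts were simulated for 45 and 30 patients (3,000 replicates). The assumptions were a mean of 2 visits per window and RR = 0.6, so the true difference is 2 × (0.6 − 1) = −0.80. Each analysis was a linear regression on arm.

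| Analysis | Mean estimate (frailty variance 1.0; 0.5) | Empirical SE (1.0; 0.5) |
|---|---|---|
| Sum of windows | −0.81; −0.79 | 0.98; 0.77 |
| Post only | −0.81; −0.80 | 0.51; 0.42 |
| Post adjusted for prior count | −0.79; −0.79 | 0.39; 0.37 |

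All three recover about −0.8. The SE of the sum is about 2.1 to 2.5 times that of the adjusted analysis (0.77/0.37 and 0.98/0.39).

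**The case against.** The strongest reply is that Table 2 never says total, sum or 12-month count. Naming a window before and a window after is at least as natural for a descriptive before-after display, or for a baseline value with a follow-up value. The sum also fits poorly with an objective about the intervention's effect on utilization. This stands. A reader might infer that the protocol fixes the outcome as visits before plus visits after, but the text does not support that. The large losses in the sum column are the cost of one permitted reading and not of a stated analysis.

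A reader might also infer that including the earlier visits biases the estimated effect. That holds for ratio and standardized effects only. The article names linear and logistic regression, and no ratio model for this outcome; on the absolute scale the loss is one of precision.

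A further tempting inference is that substance use will be compared without its baseline data, since Table 1 lists TAPS and a "Baseline survey (demographics and substance use history questionnaire") at baseline. The documents do not support this. The analysis section is silent on covariates, which an article commonly leaves to the analysis plan. TAPS is also a different instrument from the Timeline Followback used at follow-up, so a strong correlation cannot be presumed.

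Finally, this is a secondary outcome in a pilot that disclaims power for effectiveness. That limits the weight of the point. It does not answer it, because the wording that needs settling is in the published outcome definition, and a covariate list alone would not change that definition.

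**Conclusion.** The point holds as a badly specified outcome. Table 2 puts a window that randomization cannot affect into a between-arm measure, does not say what that window is for, and fits poorly with the three other descriptions of the outcome in the same article. Either reading that keeps the prior visits inside the outcome is less precise than adjusting for them. For rho from 0.2 to 0.7 the variance is 2.5 to 6.7 times as large for a sum and 1.67 to 1.18 times for a change score. A sum would also move a rate ratio of 0.70 to about 0.85 with equal window means (0.80 to 0.90 for q from 0.5 to 2). If the sponsor already intends the prior count as a covariate, nothing is lost and only the wording needs repair.

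All these figures rest on an assumed correlation and on equal variances in the two windows; the document gives neither. The consequence is limited to the precision and interpretability of an estimate that informs outcome selection for the next trial.

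**What to change.** In Table 2, define acute care utilization as the number of ED, hospital and urgent care visits in the six months after enrollment, compared between arms with the count in the six months before enrollment as a baseline covariate. This costs one line of text and one degree of freedom in the model.

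The same line should say when and from what source the prior count is taken. Table 1 schedules "TLFB (Substance Use and ED/Hospital Encounters; Follow-up visits only"), and the Table 2 row gives patient report at 2, 4 and 6 months, although the outcomes text also mentions administrative data review. The wording should be settled before outcome data are analyzed.
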